## Abstract

**Background:**

Foley catheters have been subject to limited development in the last few decades. They fulfil their basic function of draining urine from the bladder but cause other associated problems. T‐Control is a new silicone Foley catheter with an integrated fluid control valve whose design aims to reduce the risks associated with bladder catheterization by a multifactorial approach. The general purpose of this study is to determine the effectiveness, comfort, and experience of the patient catheterized with T‐Control® compared with patients with a conventional Foley catheter.

**Study Design:**

This trial is a mixed‐method study comprising a two‐arm, pilot comparative study with random allocation to T‐Control catheter or traditional Foley catheter in patients with long‐term catheterization and a study with qualitative methodology, through discussion groups.

**Endpoints:**

The comfort and acceptability of the T‐Control® device (qualitative) and the quality of life related to self‐perceived health (quantitative) will be analysed as primary endpoints. As secondary endpoints, the following will be analysed: magnitude and rate of infections (symptomatic and asymptomatic); days free of infection; indication of associated antibiotic treatments; determination of biofilm; number of catheter‐related adverse events; use of each type of catheterization's healthcare resources; and level of satisfaction and workload of health professionals.

**Patients and Methods:**

Eligible patients are male and female adults aged ≥18 years, who require a change of long‐term bladder catheter. The estimated sample size is 50 patients. Patient follow‐up includes both the time of catheter insertion and its removal or change 4 weeks later, plus the time until the discussion groups take place.

## BACKGROUND

1

Urinary bladder catheterization is a common healthcare procedure for therapeutic and diagnostic purposes,^1^ usually managed by nursing staff.^2^ Overall, 15.5% and 23.6% of hospitalized patients in Europe and the United States, respectively, received an indwelling bladder catheter, with higher rates for older patients, surgery departments, and intensive care units (45–79%).^3^

Urethral catheterization is the most common bladder catheterization in clinical practice.^4^ Although the available clinical evidence promotes intermittent catheterization as the first therapeutic option to preserve quality of life^5^, ^6^ and reduce long‐term complication risks,^7^, ^8^, ^9^, ^10^ frequently indwelling catheterization is required to avoid an additional burden for patients.^11^ In addition to the negative emotions of living with an indwelling catheter,^12^ complications such as urinary tract infections (UTIs), catheter obstruction, and recurrent bladder stones^13^, ^14^ might occur. Catheter‐associated UTIs are common, causing 80% of hospital‐acquired urinary infections,^8^, ^9^ increasing morbidity, mortality,^15^ and costs.^16^, ^17^ Moreover, the little scientific literature on the quality of life of patients living with urinary catheters emphasizes findings such as lack of autonomy, fear and anxiety, and self‐image concerns.^18^

Despite their wide use, limited improvements have occurred in the design and development of indwelling urinary catheters over the last few decades. It has been suggested, however, that a patient‐managed valve connected to the catheter outlet, instead of the conventional urine drainage bag, may lead to improvements,^19^ which enable voluntary and timely opening and bladder emptying by the patient and helping maintain bladder tone and capacity.^20^ This innovation could reduce bladder irritation because periodic filling would reduce contact with the catheter tip. Periodic valve‐regulated flushing might also decrease infection rates and valve blockage.^21^, ^22^, ^23^

T‐Control is a new silicone Foley catheter with an integrated valve to voluntarily control urine flow, which enables bladder filling and its conscious regulation and emptiness, thereby reducing mucosa irritation by contact of the catheter tip. This innovative valve controls urine flow by means of three different positions, from the proximal end of the tube. The “open” and “closed” positions regulate urine flow without other additional accessories required by the conventional Foley catheter. The third or “insertion” position, only available initially for the insertion manoeuvre, prevents unwanted urine leakage thanks to a specific built‐in membrane. T‐Control has an additional safety lock to prevent accidental opening of the catheter valve.

T‐Control has undergone and passed different biocompatibility studies, including the assessment of cytotoxicity, skin sensitization, intracutaneous reactivity (irritation), and acute, subacute, and subchronic systemic toxicity (necessary results to obtain the Conformité Europeéne marking). Beyond these preclinical biocompatibility studies, usability studies have also been performed to test the ease of professional handling of T‐Control. These confirm that an easier and safer insertion technique could be provided, while also being able to be performed by one person, which reduces the staffing needs currently recommended by clinical practice guidelines.^24^ Furthermore, patients' experience in the use of bladder catheters were comparatively evaluated with T‐Control and conventional catheters and recognized the added value and the intuitive and ease of use of T‐Control.^25^ Finally, in vitro studies have observed how T‐Control significantly prevented/delayed the formation and growth of biofilm during the first 5 days, compared with conventional Foley‐type catheter.^26^ In addition, another pilot clinical study is currently being carried out with the T‐Control catheter in patients with acute urinary retention (NCT05643950), for which the first results are expected to be obtained at the end of the first quarter of 2024.

This clinical trial protocol shares the methodology to make progress in regard to the process of generating evidence on the effectiveness, safety, and cost‐effectiveness of T‐Control and to improve clinical and self‐perceived health outcomes by patients, compared with conventional catheters currently used. In addition, this trial aims to generate information on the potential contribution of T‐Control to improve the sustainability and solvency of the healthcare system.

## STUDY DESIGN

2

### Trial design and trial setting

2.1

This trial is a mixed‐method study comprising a two‐arm, pilot comparative study with random allocation to T‐Control catheter or traditional Foley catheter in patients with long‐term catheterization and a study with qualitative methodology, through discussion groups.

For the quantitative study, the sample of patients will be recruited in the urology service of Hospital 12 de Octubre. The identification of patients eligible to participate will be carried out by members of the urology service staff. The subjects included in the quantitative study who have completed the follow‐up will be invited by the urology clinic researcher to participate in the qualitative study.

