## ENDPOINTS

3

The general purpose of this study is to determine the effectiveness, comfort, and experience of the patient catheterized with T‐Control® compared with patients with a conventional Foley catheter, by evaluating patients with long‐term urinary catheters.

Primary endpoints are as follows:
To analyse, through qualitative techniques, the comfort and acceptability of the T‐Control® device for the patient framed in the course of the disease, identifying preferences and training and information needs for the use of the device; andTo analyse and compare the degree of satisfaction and levels of self‐perceived health‐related quality of life of patients with both types of catheters.

Secondary endpoints are as follows:
To assess the preliminary effectiveness of T‐Control versus a common Foley catheter, by comparing the magnitude and rate of infections (both symptomatic and asymptomatic) due to the catheter among long‐term catheterized patients. Additionally, evaluate the effectiveness of T‐Control by comparing the days free of infection on the 28th day after catheterization;To compare the indication of antibiotic treatments associated with catheter use between the conventional Foley‐type catheter and the T‐Control device;To determine the biofilm formed in the catheters and identify the microorganisms that form this to evaluate its relationship with the onset of symptomatic and asymptomatic infections as well as different adverse events;To compare the number and relevance of adverse events related to bladder catheterization between T‐Control and the traditional Foley catheter;To assess the preliminary cost‐effectiveness of T‐Control versus the traditional Foley catheter from the public healthcare services perspective; andTo measure and compare the level of satisfaction and workload perceived of health professionals with both types of catheterization by means of a questionnaire at the end of the study.

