**FIGURE 1 bco2313-fig-0001:**
[figure not shown]
Flow diagram describing the participant timeline through the clinical trial. EQ‐5D‐5L, EuroQol questionnaire—five dimensions—five levels; QoL, quality of life; UTI, urinary tract infections.

After catheter insertion, participants and their family, friends, or other informal caregivers will receive information about wearing an indwelling urinary catheter and specific information about the device randomly inserted, the standard Foley or the T‐Control catheter (Data S2). Standard catheter care is permitted during the trial both managed by the participants or participants' caregivers. In addition, patients will receive an incident diary (Data S4) in which they can record any incident during the bladder catheterization period. Four weeks after indwelling bladder catheter insertion, patients will be contacted by the urology outpatients department for a follow‐up visit, during which the study catheter will be removed and Clinical Data Notebook completed (Data S3).

Finally, after the follow‐up visit, a patient subgroup will take part in the discussion groups to evaluate their acceptability of the device used as well as their experiences, preferences, and needs (at which point their contribution to the research will finish).

Health professionals who have participated in the study will complete at closure, and after signing the informed consent form, a survey where they will evaluate their level of satisfaction and workload perceived for both types of catheters included in the study (Data S7).

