#### Criteria for discontinuing or modifying allocated interventions

5.2.1

Reasons for going off or discontinuing the trial are as follows:
Adverse events that may compromise the patient's safety;Need for antibiotic treatment for a reason unrelated to the use of a bladder catheter;The patient's refusal to continue (in the event that, according to clinical practice, they still needed to carry an indwelling bladder catheter, the T‐Control catheter would be exchanged for the conventional Foley‐type catheter); andDeath.

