### Sample size determination

5.3

The sample size for the quantitative primary endpoint “degree of satisfaction and levels of self‐perceived health‐related quality of life of patients” has been calculated in terms of standardized differences through Cohen's delta. Assuming a significance level of 2.5%, given that the endpoint is composed of two different questionnaires (EuroQol‐5D‐5L [EQ‐5D‐5L] and Catheter‐related quality of life questionnaires), and expecting large differences (0.95) between groups, a sample size of 25 per group would be enough, taking into account a dropout rate of 5%.

Regarding the qualitative primary endpoint, it is expected to reach information saturation with a maximum of four discussion groups composed of between 8 and 10 participants (a total of a maximum of 40 subjects), so the calculated sample size is considered sufficient.

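### The T-Control acceptability co-primary draws its discussion groups only from patients who completed follow-up, so those who stop the device early have no stated route in; section 5.3 also does not show sufficiency in terms of T-Control users.

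*Protocol article*

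**What the plan says.** All references are to the protocol article.

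- **Endpoint (section 3).** The first primary endpoint is worded as "To analyse, through qualitative techniques, the comfort and acceptability of the T"-Control device. The matching outcome in section 5.4.1 names the same device and adds possible future improvements to it.
- **Who is invited (section 2.1).** "The subjects included in the quantitative study who have completed the" follow-up are invited by the urology clinic researcher. No arm is named.
- **When, and about what (section 5.2).** After the follow-up visit, "a patient subgroup will take part in the discussion groups to evaluate their acceptability of the device used".
- **Who leaves (section 5.2.1).** Reasons for discontinuing include adverse events that may endanger the patient and "The patient's refusal to continue". For a refuser who still needs an indwelling catheter, the T-Control "catheter would be exchanged for the conventional Foley" type.
- **Size (section 5.3).** Saturation is expected with a "maximum of four discussion groups composed of between 8 and 10 participants (a total of a maximum of 40 subjects"). The conclusion drawn is: "a total of a maximum of 40 subjects), so the calculated sample size is considered sufficient". The calculated size is 25 per group, allowing for 5% dropout.
- **Early leavers elsewhere.** Section 5.6 keeps their data and promises a substudy analysis. Section 5.7 bases the analysis population on all eligible randomised patients, with 4-week completers as an additional analysis. Neither section mentions the discussion groups.

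**The concern.** Acceptability is the outcome most closely tied to whether a patient is willing to keep using a device. If the sampling frame for that outcome is defined by having completed follow-up, membership of the frame depends on the thing being studied. Section 5.2.1 foresees patients who give up T-Control, and section 2.1 then leaves them outside the groups. The quantitative analysis is protected by starting from all randomised patients. The qualitative co-primary has no equivalent.

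At stake is the range of views. Section 5.4.1 wants to learn which aspects participants find most and least beneficial, and what training and information they need. A patient who stopped because of the device may hold the sharpest negative evidence. That evidence is hard to recover once the groups have been held without the patient.

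The second issue is the denominator. A primary endpoint about one device is declared adequately sampled by reference to a total in which only half the patients wear that device.

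**Working it through.** **Inputs.** 50 patients (abstract); 1:1 allocation (section 2.3); 25 per group, 5% dropout, standardised difference 0.95, significance level 2.5%, at most four groups of 8 to 10 (all section 5.3).

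**1. The plan's own figures.** Power and sidedness are not stated. With two-sided 2.5%, a t-based two-sample comparison and an assumed 80% power, the requirement is 23 per group; 23 / 0.95 = 24.2, which rounds up to 25. The discussion-group ceiling is 4 × 10 = 40, and the low end of four groups is 4 × 8 = 32. Both stated figures reproduce.

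**2. Does the invitation rule exclude early stoppers?** The text does not say so outright; it follows from two sections.

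- Section 2.1: only those who completed follow-up are invited.
- Section 5.2.1: refusal and safety-compromising events are reasons for leaving the trial.

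A patient who has left the trial has not completed follow-up and so is not invited. No other section opens a route: section 5.2 places the groups after the follow-up visit, and section 5.6 deals only with data already collected.

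**3. How many patients?**

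- Expected early leavers on T-Control at 5%: 25 × 0.05 = 1.25.
- Chance of at least one, assuming independence: 1 − 0.95^25 = 0.72.

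These count every reason for leaving, including death and unrelated antibiotic use, so device-related stoppers are a subset. The 5% is the plan's figure. The effect of higher early stopping in the T-Control arm is illustrated below; the 10% to 30% rates are assumptions.

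| Early leaving | Leavers of 25 | Completers of 25 |
|---|---|---|
| 5% (plan) | 1.25 | 23.75 |
| 10% | 2.5 | 22.5 |
| 20% | 5 | 20 |
| 30% | 7.5 | 17.5 |

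**4. Does the sufficiency statement hold?**

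- Both arms: 50 × 0.95 = 47.5 expected completers. Uptake needed is 32 / 47.5 = 67% for four groups of 8 and 40 / 47.5 = 84% for four groups of 10.
- T-Control only: 25 × 0.95 = 23.75, about 24. Two groups of 8 to 10 need 16 to 20, which fits. Three groups of 8 need 24, which is essentially every completer. Four groups need 32 to 40, more than the 25 allocated.
- T-Control completers as a share of the ceiling: 23.75 / 40 = 59%; as a share of the low end, 23.75 / 32 = 74%.

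Since 40 exceeds 25, the statement in 5.3 relies on both arms together.

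**The case against.** Several points on the other side are sound.

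- **The exclusion is inferred.** The heading of section 5.2.1 also covers modified interventions, and the article does not say whether a patient exchanged to a Foley misses the 4-week visit. This stands as a caveat. It also shows that the text leaves the matter open when one sentence would settle it.
- **Early leavers are not ignored.** A reader might infer that they are never heard. The documents do not support that: they hold an incident diary, their data are retained, and a substudy analysis is promised. None of this places them in the discussion groups, which are the source for this co-primary.
- **Completers can be critical.** Someone may wear T-Control for four weeks, dislike it and say so. The selection is therefore towards patients who tolerated the device, not only those who approved of it.
- **The planned number is small.** About one patient is expected. That limits the size of the problem, though in qualitative work a single stopper can add a theme that no completer raises.
- **The sample size.** A reader might infer that the discussion-group sample cannot be reached. It can: 40 is a ceiling for saturation, not a target; section 2.1 names no arm; section 5.2 speaks of the device used; and about 47.5 completers supply 32 to 40 people at 67% to 84% uptake. Nor can one say that most of the four groups could not be T-Control users, since two or even three of the four could be. Foley users can also offer contrast on preferences and the course of disease, though they cannot report experience of wearing T-Control in this trial. How arms are split among groups may be in the full protocol and is not counted here as an omission.

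**Conclusion.** The point holds in a limited form. As written, the invitation rule in section 2.1, read with section 5.2.1, gives patients who stop T-Control early no stated way into the groups on which its acceptability co-primary rests. The resulting account is selected towards those who tolerated the device. The expected size at the plan's 5% dropout is about 1.25 of 25 patients for all reasons, with a 72% chance of at least one if departures are independent. It grows with poor tolerability, which is when the missing views matter most. The conclusion assumes that leaving the trial means not completing follow-up.

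The secondary point is narrower. The sufficiency statement in section 5.3 is valid for both arms combined but does not show sufficiency for an endpoint about T-Control, on which at most 25 patients (about 24 completers) can speak from experience in this trial. Whether two or three groups would reach saturation is a judgement the article does not make; it may well be enough.

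This is a cheap improvement to a primary endpoint. It does not invalidate the design.

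**What to change.** 1. **Section 2.1.** Replace the completer condition with an invitation to every patient in whom a T-Control catheter was placed, including those who stopped early and are able and willing to take part. Keep the existing invitation for Foley-arm completers if their contrast is wanted.
2. **Reporting.** State how many T-Control patients stopped early, how many of them were invited, and how many took part.
3. **Section 5.3.** State the sufficiency of the qualitative sample for the T-Control endpoint in T-Control users: about 24 expected completers, enough for two groups of 8 to 10, or three of 8 at full uptake, plus any early stoppers. The ceiling of 40 can stay as the figure for both arms.

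The cost is two wording changes and a few extra invitations by the existing qualitative team. Randomisation, the quantitative sample size and clinical management are untouched. The change to section 2.1 is best made before the groups are convened, because stoppers are harder to reach later.

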### Recruitment

2.2

Patients eligible to participate will be identified by the health professionals responsible for the study. All those patients who require a change of long‐term bladder catheter will be invited to participate and will be interviewed in an initial visit, where the inclusion and exclusion criteria will be checked, and the patients or their relative/caregiver (if necessary) will receive information about the study, will be invited to participate in the study, and will request their consent agreement, including the subject on the study's registration sheet.

### Random assignment

2.3

Participants will be assigned 1:1 to one of the two trial arms of the quantitative study by a local research team member using a centralized computerized randomization system (RAND2 software, The MathWorks Inc, Natick, USA, administered by the data management team, depending on the contract research organization [CRO]).

The blinded allocation sequence is concealed by the use of a centralized computerized randomization system. The personnel responsible for catheter insertion will enrol subjects on the randomization system.

The patient's identifying number will be consecutively assigned, and inclusion in the intervention group or control group will be carried out through the randomized numerical distribution generated by a random online generator.

### Blinding

2.4

It will not be possible to blind the study arm for the trial subjects, the health professionals, the research team involved, and the monitoring team. Data analysis will be blinded to the intervention arm as well as the laboratories that will analyse the urine and catheter samples.

In the event of adverse events that may compromise the patient's safety, data may be unmasked by means of the unique code given to each participant.

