#### Intervention arm: T‐Control catheter

5.1.1

The T‐control catheter is a flexible, silicone tube with an inflatable balloon at the distal tip, a polytetrafluoroethylene (PTFE) membrane integrated into its body, and a sliding fluid control valve. The valve, built into the catheter, provides additional functions to the catheter, such as turning urine flow on and off after insertion (functions currently provided by accessories such as caps or valves) and controlling urination during the insertion process (function not provided by any other device). Accidental loss of urine can thus be avoided from the first moment of use until its withdrawal. In addition, it has a safety cap that reduces the possibility of accidental valve movements before use or during transport and fixing. The design has been developed in such a way that, once inserted, it facilitates autonomous use even for the elderly or patients with limited manual dexterity. The device is sterile and single‐use, like any conventional Foley catheter.

The continuous use of a single device of T‐Control cannot exceed 30 days. The cumulative use for each type of T‐Control device can exceed 30 days.

T‐Control is manufactured, sterilized, and packaged by the subcontracted company Conod Medical Co., Ltd under the specifications of Rethink Medical and under its quality standards, as well as its accessory holder, also manufactured and packaged by the same subcontracted company.

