#### Control arm: Foley catheter

5.1.2

Silicone Foley catheters are transurethral balloon catheters used to treat bladder emptying disorders, as well as drain urine from the urinary tract, continuous fluid irrigation, and/or medication administration. It is suitable to be used for a prolonged period of no more than 29 days and in Urology, Internal Medicine, Surgery, Obstetrics, and Gynaecology Services.

For this arm, conventional two‐way silicone Foley‐type catheters will be used. They consist of a body, drainage funnel, inflation funnel, and balloon valve. The product is sterile and single use.

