##### Self‐perceived health‐related quality of life

The following instruments are administered to patients:
EQ‐5D‐5L^27^: This is a generic health‐related quality of life questionnaire that evaluates five domains: mobility, self‐care, usual activity, pain/discomfort, and anxiety/depression. Each domain is scored on a 5‐point scale, which yields a descriptive system that can be combined into a five‐digit number reporting the patient's state of health. Each EQ‐5D‐5L health state can be converted to a single summary index by applying a formula that attaches weights to each level in each dimension. A number of formulae or value sets are available for different countries, based on the valuation of EQ‐5D health states from general population samples. In this study, the value set estimated for Spain by Ramos‐Goñi et al.^28^ will be used. After applying these weights, the range of the summary index is 1 (perfect health) to 0 (health state equivalent to death). Negative values represent health states considered to be worse than death. The questionnaire also includes a visual analogue scale where responders are asked to indicate their health status on the day of the interview, ranging from 0 (worst possible health) to 100 (best possible health).Catheter‐related quality of life questionnaire: To evaluate the specific health‐related quality of life for long‐term catheterized patients, Rethink Medical has developed two specific instruments created in the context of this project based on the experience of our previous studies (Patient's workshop).^25^ The first one (Data S5), administered during the initial visit, consists of 47 questions, related to the patient's experience and journey with catheterization before the study, as baseline data. The questions are related to the type of catheter and accessories used, the experience of catheterization, emotions felt at the beginning (right from the moment of the prescription), satisfaction and comfort with the catheter, complications associated with catheter use, usability and complications associated with accessories and changes in the personal habits caused by the catheter's use, and how these issues have affected their lives. The second one (Data S6), administered during the follow‐up visit, consists of the same questions as the first one (but referred to the catheter and accessories used during the study) plus four questions related to information received when catheterized for the first time (total 51 questions). In order to quantitatively evaluate the answers, statements will include single answers with scores on a scale from 0 to 10, 0 to 5, and 0 to 4 for both questionnaires. The questionnaire devised by Rethink Medical is expected to be validated during the clinical study in conjunction with another study specially designed for its validation.

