##### Determination of the biofilm formed in the catheters and identification of the microorganisms present

The catheter removed will be sent to the laboratory, and with the help of sterile gloves and scissors, a 1 cm‐sized fragment corresponding to the part below the balloon will be cultured for each catheter to assess whether biofilm is present or absent. The microorganisms forming the biofilm will be quantified as CFU per catheter piece. These microorganisms will also be identified by means of MALDI‐TOF‐type mass spectrometry to establish statistical relationships with those identified in the urine cultures. In the event that during the course of the 14 days in which the patient will be catheterized, he receives antibiotic treatment due to a UTI, this will be taken into account when analysing the results obtained in the catheter's biofilm determination.

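### The protocol says the catheter laboratory is blinded, but it sends the removed catheter, with its visible built-in valve, to that laboratory before the test piece is cut

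*Protocol article*

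**What the plan says.** Section 2.4 (Blinding) accepts that participants, health professionals, the research team and the monitors cannot be blinded. It then makes two claims in one sentence: "Data analysis will be blinded to the intervention arm as well as the laboratories that will analyse the urine and catheter samples".

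Section 5.4.2, in the part on biofilm, describes what happens to the catheter: "The catheter removed will be sent to the laboratory, and with the help of sterile gloves and scissors", a piece 1 cm in size is taken. That piece is defined as the "fragment corresponding to the part below the balloon will be cultured for each catheter to assess whether biofilm is present or absent". Organisms are counted as CFU per piece and identified by MALDI-TOF mass spectrometry.

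The two devices are described in sections 5.1.1 and 5.1.2. Of T-Control: "The valve, built into the catheter, provides additional functions to the catheter". Of the conventional catheters: "They consist of a body, drainage funnel, inflation funnel, and balloon valve". The Background adds, for T-Control, "This innovative valve controls urine flow by means of three different positions, from the proximal end of the tube".

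**The concern.** A participant code on a label hides the allocation only if the specimen does not show it. Here the specimen is the device under test, and the two devices differ in a part that anyone can see.

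The trial is open-label for everyone else, so laboratory blinding is one of the few safeguards it has. The Background also reports in vitro results in which T-Control prevented or delayed biofilm over the first 5 days. Staff who recognise the device may therefore expect a result in a particular direction. Handling, plating and calling biofilm present or absent are all human steps.

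If the procedure runs as described, a report that the catheter laboratory was blinded would misstate how the biofilm outcome was obtained.

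**Working it through.** The document gives no figure for this point, so the check sets the relevant sections side by side.

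1. **What is claimed.** Section 2.4 covers both the urine and the catheter samples, so the claim has to hold for each.
2. **What reaches the laboratory.** Section 5.4.2 sends the removed catheter and describes the cut after the sending. The text does not use the word whole, but intact arrival is the natural reading of that order. No earlier cut, no covering of the valve end and no coding of the piece is described.
3. **Whether the catheter shows the arm.** Section 5.1.1 describes a sliding flow valve that is part of the T-Control catheter. The component list for the control catheter in 5.1.2 has only a balloon valve and no flow valve. An intact catheter therefore identifies its arm on sight.
4. **Whether the cultured piece shows the arm.** The piece comes from just below the balloon, and 5.1.1 places the balloon at the distal tip. The Background places control of the valve at the proximal end. A 1 cm piece from below the balloon should therefore not include the valve. Both catheters are silicone. Once separated and coded, the piece could plausibly be read blind, although the document does not compare the tubing for colour or markings.
5. **Who is affected.** The planned sample is 25 per group, so 2 × 25 = 50 catheters at most. Each one is recognisable to the person who receives and cuts it.
6. **Urine samples.** Section 5.4.2 sends 5 to 10 mL of urine in a sterile container. Urine does not show the device, so this half of the claim stands.

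Steps 1 to 3 conflict for the person who receives and cuts the catheter. Step 4 shows that the conflict can be removed without changing what is measured.

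**The case against.** The strongest reply is that the article does not say who cuts and who reads. One technician could cut and code the piece while another cultures and counts without knowing the arm, which would satisfy section 2.4. This stands in part. It means that unblinding of the plate reading is not proven, and that a statement that laboratory masking is nil would go too far. It does not rescue the text, because no such division of work is described and the blinding claim makes no exception for the person who cuts.

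A second reply is that little is at stake. Biofilm is a secondary outcome. The site and size of the piece are fixed, and CFU counts and mass spectrometry leave limited discretion. The objective in section 3 is framed as a relation between biofilm and infections or adverse events, with no explicit comparison between arms. All of this stands and limits the consequence. It does not make the statement in 2.4 true.

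A reader might also infer that the analyst is unblinded. The questionnaire is described thus: "The questions are related to the type of catheter and accessories used". The follow-up version "consists of the same questions as the first one (but referred to the catheter and accessories used during the study"). The document does not support that inference:

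- It does not say that these items enter the analyst's file.
- Section 5.4.1 bases the quantitative evaluation on scored statements.
- Section 5.5 gives the statistician access by participant code only, and section 5.7 says that the analyst will not know the group.
- Which fields are transferred is commonly settled in the analysis plan or a data-management plan.

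**Conclusion.** The point holds for the catheter samples only. The handling in section 5.4.2 does not deliver the blinding that section 2.4 claims for whoever receives and cuts the catheter, and nothing described restores it before culture and reading. This is a contradiction between two stated procedures, not a detail that the article has left to a fuller document.

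Up to 50 catheters are affected. The effect on biofilm presence or CFU cannot be quantified from the document. It is probably limited, because the piece is fixed and the readout largely instrumental. Infection magnitude and rate, which rest on urine culture, are untouched, and so are the primary endpoints.

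The conclusion assumes that the catheter arrives uncut, which is the natural reading of the text but not an explicit statement. It does not extend to the urine laboratory or to the data analyst.

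**What to change.** In section 5.4.2, state that a person who does no culture or reading cuts the fixed 1 cm segment below the balloon aseptically and passes on only that segment, in a coded sterile container. This can be a laboratory staff member, or the already unblinded research staff at catheter removal. The person who cuts will still know the arm, but the fixed site and size leave little room for choice, and the steps that produce the result become blind. Before relying on this, check that the bare segments of the two catheters look alike.

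If this cannot be arranged, restrict the laboratory claim in section 2.4 to urine samples and report the biofilm outcome as not blinded.

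The first option costs one line in the procedure and one extra handling step. If the cut is made outside the laboratory there is a small contamination risk, which would act directly on the biofilm result. Cutting by a second person inside the laboratory avoids that. The second option costs one sentence.
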